**Study 2: Determine peripheral micro- and macrovascular endothelial function in study participants before and after TRE:**

Changes in microvascular blood flow will be measured in the nailbeds of the right hand in response to a 5-minute blood flow occlusion in the brachial artery using a sphygmomanometer cuff inflated to the level of current systolic blood pressure plus 50 mmHg, or a maximum of 200 mmHg using the **laser speckle contrast imaging** (Perimed). The magnitude of the response is a reliable indicator of endothelium-mediated microvascular dilation.

We will also assess macrovascular endothelial function using the gold-standard method of flow-mediated dilation (FMD) in the brachial artery using an 8-12 MHz transducer (Phillips Affinity 70, or other). Reactive hyperemia will be induced by 5 minutes of forearm occlusion with a sphygmomanometer cuff inflated to the level of current systolic blood pressure plus 50 mmHg, or a maximum of 200 mmHg. After the cuff is deflated, changes in the diameter of the brachial artery will be recorded at 20-, 40-, 60-, and 80-seconds, and FMD will be calculated as maximal relative diameter gain normalized to baseline [27].

We will also assess **arterial stiffness** using the pulse wave analysis approach (SphygmoCor, Atcor medical, Itasca IL, or similar). We will also perform a short (approximately 5 minutes long) recording of the sublingual vasculature using the **GlycoCheck** device (Microvascular Health Solutions) – the system is equipped with a high-resolution camera that is capable to evaluate capillary density, blood volume, blood flow and red cell velocity, endothelial glycocalyx function.

**Study 3: Evaluate performance in different cognitive domains using a comprehensive battery of cognitive tests.** To assess different cognitive domains, a selection of tests from the NIH toolbox will be used as previously described [28, 29]. These batteries of tests are optimized to detect age-related changes in cognition and assesses reaction time, practice (sensorimotor function and comprehension), attention (processing and psychomotor speed, sustained attention), memory (visual episodic and verbal recognition memory, attention, short-term memory, visual recognition), and executive function (working memory and strategy).

**Study 4: Blood draw (venipuncture).** We will perform a blood draw via venipuncture and collect up to 40mL of blood for each visit.

Our prediction, based on our preclinical preliminary data and other laboratory's findings, is that serum isolated from study participants that have best adhered to a 6-month long TRE regimen will contain several circulating factors that will induce SIRT1 activation in commercially available human CMVECs. This study will simulate *in vitro* the microenvironment and the circulating factors in which cerebral

endothelial cells are exposed to *in vivo* within the study participants. To measure SIRT1 in CMVECs, we will perform a nuclear extraction in the resulting endothelial cells followed by immunoprecipitation of SIRT1. SIRT1 activity in the samples will be measured using the Cyclex SIRT1 Deacetylase Fluorimetric Assay as described [30]. Specific activity of SIRT1 will be assessed by measuring time-dependent changes in fluorescence intensity, normalized to protein concentration determined by the Bradford method on the nuclear extracts. Deacetylase activity of SIRT1 will be measured using the PNC1–OPT assay, which provides a quick and reliable method to measure SIRT1 deacetylation activity without specialized equipment [31]. Alternatively, measurements of deacetylation of Sirt1 substrates such as p53 and histone H4 can be performed as described [32].

NO production by CMVECs in response to exogenously administered ATP will be assessed by flow cytometry. Cellular production of reactive oxygen species (ROS) will be measured in detector CMVECs by flow cytometry using the redox sensitive fluorescent dye DHE [15].

In addition, a separate set of plasma, serum samples, whole blood, and blood cells (including white blood cells) will be stored for future analyses.

Once stored in tissue repository bank, blood samples may be used for future studies, including genetic testing.

**Study 5: Examine the mechanisms underlying TRE using functional magnetic resonance imaging (fMRI).** We will also use fMRI to assess brain changes, including the quantification of cortical reorganization. Using fMRI, we will determine the changes in Blood-Oxygen-Level dependent activation. We will compare these neurophysiological parameters before and after treatment. Participants will perform 2 fMRI visits at the Laureate Institute for Brain Research (Tulsa, OK). fMRI recordings will be performed during a standardized cognitive, sensory and/or motor task.

***Future studies:*** Identifiers might be removed, and the de-identified information may be used for future research without additional informed consent from the subject.

**E. Chart Review**  
N/A.

**F. Biospecimens**

As part of our study, we will collect blood samples, including whole blood, plasma, serum, and blood cells (e.g. white blood cells). Biospecimens will be collected prospectively, at the time of 1st and 2nd visit. All subjects will be assigned study ID, and all biospecimens will be labeled with corresponding study ID.

Biospecimens will not be used for commercial profit. While it is not planned at the moment, the research may include genetic analysis, such as transcriptomics and single-cell sequencing analysis to determine the effect of TRE on cellular function.

**G. Banking/Repository/Database**

All biospecimens will be stored in the Translational Geroscience Laboratory in -20 or -80 freezers, specifically purchased to store human biospecimens. All biospecimens will be stored until used. All biospecimens will have study participant ID label and only study personnel will have access to the identifiable data.

Biospecimens may be shared with researchers upon request and upon availability without providing identifiable information.

All electronic data associated with this study, including linkable data to the biospecimens and potential future electronic data from biospecimen analyses will be stored on encrypted drives (OUHSC shared drive and encrypted external hard drives).

**H. Inclusion / Exclusion Criteria**

| Table 1: Inclusion criteria:                                                                                                                                                                                                                                                                                                                                                                                                            | Exclusion criteria:                                                                                                                                                                                                                                                                                                                                                                                                                                                                                                                                                                                                                                                                                              |
|------------------------------------------------------------------------------------------------------------------------------------------------------------------------------------------------------------------------------------------------------------------------------------------------------------------------------------------------------------------------------------------------------------------------------------------------|-------------------------------------------------------------------------------------------------------------------------------------------------------------------------------------------------------------------------------------------------------------------------------------------------------------------------------------------------------------------------------------------------------------------------------------------------------------------------------------------------------------------------------------------------------------------------------------------------------------------------------------------------------------------------------------------------------------------------|
| 
 
• Age <math>\geq 55</math> and <math>\leq 80</math> years of age
 
• Adequate hearing and visual acuity to participate in the examinations
 
• Ability to read and write in English
 
• Competence to provide informed consent
 
• Mini-Montreal Cognitive Assessment score <math>\geq 12</math>
 
• Mini Nutrition Assessment score <math>\geq 12</math>
 
 | 
 
• Vision or hearing impairment that would impair the ability to complete study assessments
 
• Active CNS disease including multiple sclerosis, uncontrolled seizures, active brain cancer
 
• Cerebrovascular accident other than TIA within 60 days prior to Visit 0
 
• Major psychiatric disease, including major depression not currently controlled on medications, and alcohol or drug abuse
 
• Diabetics prescribed sulfonylureas, meglitinides, and insulin
 
• Any other medical condition which, in the opinion of investigator, would render the patient inappropriate or too unstable to complete the study protocol
 
 |

\* If the subject is not eligible for an fMRI or does not want to participate, we will not perform this assessment as fMRI is not required for study eligibility and it is only used as a secondary outcome. Similarly, if a participant does not want to participate in a DXA scan, we will not perform this assessment as it is not required for study eligibility.

#### **I. Gender/Minority/Pediatric Inclusion for Research**

Both male and female participants will be enrolled in each group, and analysis will account for sex as a biological variable.

#### **J. Recruitment and Enrollment**

Patient recruitment will be performed via advertisement through the Oklahoma Clinical and Translational Sciences Institute, via an advertisement in community newspapers and journals that target older adults such as “Senior Living” or other, through the pool of study participants from an ongoing clinical study on aging led by [name], through collaborative ties with the Section of Geriatric Medicine, through social media such as Facebook ads, or through other means. We will also use MyChart messaging to advertise the study to potential subjects to increase participant diversity (MyChart message write-up attached to application). Potential subjects may be identified via EPIC’s Best Practice Advisory (BPA) system. While the patient is being seen for a standard of care visit, a notification may be sent to the provider via EPIC’s BPA indicating that the patient may qualify for the research study. This notification would contain a small explanation of the study, why the patient qualifies, and ask the provider to mention it to the patient and indicate the patient’s interest/disinterest. Should the provider mark the patient is “interested”, the study team will be automatically notified and reach out to the patient for initial contact. Electronic health records may also be screened to identify potential study participants who have previously agreed to be contacted for future research. These identified patients would then be contacted by key study personnel via telephone utilizing the approved phone script.

Interested subjects will speak directly to study personnel at the site of physician’s office and then contact us to schedule an outpatient visit in the Translational Geroscience Laboratory at the University of Oklahoma Health Sciences Center. The protocol in details addressing all the questions that might appear during the first contact or at the first visit at the Translational Geroscience Laboratory. All subjects must demonstrate understanding of the study prior to beginning study procedures, and will be given as long as they need to decide whether to participate. All subjects may withdraw their consent at any time, for any reason.

All subjects will be given as long as they need to decide whether to participate. All subjects will also be asked to answer the following questions prior to signing the consent:

- 1) Please describe the study procedures.
- 2) Why are you doing this study?
- 3) What will happen if you decide not to do this study?

By answering these questions, the subject will be able to demonstrate that they understand the study procedures and that their participation is completely voluntary.

**K. Risks and Benefits**

**Risks associated with assessment methodologies.**

This study carries no more than minimal risk that is otherwise associated with routine medical care and testing.

There is a small but minimal risk of loss of confidentiality. All efforts will be made to protect participant confidentiality as outlined below.

There is a small chance that these results could cause psychological stress for these individuals, and study staff will try to mitigate this risk by demonstrating empathy and support with referral to an appropriate healthcare provider.

The two neurovascular coupling studies utilized in this study are noninvasive. There is a small chance of mild physical discomfort with fNIRS and DVA, and participants may elect to discontinue these procedures if they experience discomfort.

As previously described in IRB protocol #9384: "Flickering light used for the dynamic vessel analysis might trigger a seizure if the participant has photosensitive epilepsy. Individuals with history of seizures will be excluded from this assessment. In addition, dilation of the pupil may lead to an acute angle-closure glaucoma attack. Only participants with a non-occludable angle and with no optic neuropathy (based on the slit lamp examination, these procedures do not require pupil dilation) will receive the topical tropicamide. The participants will be asked to seek immediate medical attention if they experience symptoms of glaucoma attack (severe ocular pain and redness, decreased vision, colored halos in combination with headache, nausea and vomiting)."

Participants will be asked to have a designated driver assist them with transportation home after the study and will be advised that they may have visual difficulty limiting their ability to work for several hours after completion of the dilation.

There are no known harmful side effects associated with temporary exposure to the strong magnetic field used by MRI scanners. However, there are important safety concerns to consider before performing or undergoing an MRI scan. For that reason, a standard Safety Form will be filled out by the radiation technician that records the subject's medical history relevant to scanner safety. Additional sources of risk include the following:

- The subject may experience discomfort being in the confined environment of the scanner.
- The strong magnetic field will affect electronic, magnetic, and metal devices that subjects carry with them or that have been implanted in the subject's body. These will be assessed prior to scanning, and the session will be cancelled if safety criteria are not satisfied.
- Claustrophobia: Some subjects may get anxious in confined spaces.
- Peripheral Nerve Stimulation effects: Occasionally, some subjects may experience muscle twitching or paresthesias, especially in the torso.
- Dizziness: Some individuals may experience light-headedness while in the scanner or when rising from the MRI gurney too rapidly.
- Hearing: MRI scanning produces a loud high frequency tone that can cause hearing damage if appropriate hearing protection is not used. Regarding acoustic noise associated with MRI, all the subjects scanned will receive ear protection (earplugs and/or headphones).

If the subject is not eligible for an MRI at the time of the study, we will not perform this assessment as MRI is not required for study eligibility and it is only used as a secondary outcome.

DXA scans use a minimal amount of radiation (lower than a standard X-ray) and pose no more than minimal risk.

**Benefits of the study**

Participants may derive personal satisfaction by contributing to the overall knowledge on the mechanisms involved in neurodegeneration. They may also receive directly benefits by learning more about their general health, cognitive function and neurovascular function in response to cognitive tasking. If during a study visit, an incidental medical problem is newly uncovered, the PI team will contact the participant's physician after obtaining permission from the subject. Incidental findings from the optional MRI scan will be reviewed by the study team neurologist ([name] [name]). Findings from this study will also provide important knowledge to caregivers that may result in modifications to the implemented care and improve clinical outcomes.

**L. Multiple Sites**  
N/A

**M. Statistical Methods**

There are currently no published data available on the effect of TRE on NVC responses in healthy young and older adults. Data obtained from this project will be used as preliminary data for an NIH application.

*Functional near infrared spectroscopy and dynamic retinal vessel analysis:* fNIRS data will be analyzed using a pipeline based on General Linear Model (GLM) approach created using the Brain AnalyzIR toolbox. After conversion of optical densities to change of hemoglobin concentration using the Beer-Lambert law, pre-whitening of data with an autoregressive model-based algorithm, and a discrete cosine transformation using high-pass filter, design matrices will be convolved with a canonical hemodynamic response function to predict brain activation. Parameter estimates (beta-weights), scaling the predictors, will be then used for group level statistics. Group level statistics will be performed using a repeated measures mixed effects model. The model will be defined in a Wilkinson-Rogers formula of 'beta ~ -1 + Group +(1|Subject)'. Output of the mixed effects model statistics will be used for a t test. Increased activation/NVC responses will be considered significant where false discovery rate corrected  $q < 0.05$ . When appropriate, beta values from corresponding channels to the cognitive task will be summarized using mean ( $\pm$ SEM) by group and study visit. We will use repeated measures mixed effects models (with a random subject effect) to assess the main effect of group (TRE vs. control) on NVC responses.

For DVA analysis, each participant will be evaluated for mean maximal arteriolar dilation and mean maximal venular dilation in response to flicker light stimulation. The statistical mean of 3 consecutive examinations will be calculated for each subject and each evaluated parameter as previously described. Data will be summarized using mean ( $\pm$ SEM) by group and study visit. We will use GLM with control and TRE treatment as between-group factor, and Visit 1 and Visit 2 as repeated measures (within group) factor. For post-hoc analysis, we will perform the Bonferroni test. The level of significance will be regarded as  $p < 0.05$ .

For EEG analysis, the power spectral density of EEG records (obtain during n-back stimulation) will be estimated using the Welch's method and then averaged across 14 channels of the Emotive EPOC research instrument. Spectra will be plotted in a semilogarithmic graph as a function of EEG frequency. For channel-wise comparison, Lilliefors tests will be applied to verify normality of the data. For normally distributed data,  $F$  test will be then used to confirm equality of variances between groups, and the two-sample  $t$  test or the Welch-corrected  $t$  test will be applied for equal or unequal variances, respectively. For not normally distributed data, a Mann-Whitney  $U$  test will be used for group comparison. The false discovery rate (FDR) method of Benjamini and Hochberga will be applied to control for multiple comparisons.

*Peripheral endothelial function:* For analysis of micro- and macrovascular endothelial function, all data will be corrected for mean arterial pressure. Laser speckle data will be normalized to an average of 3 measurements of skin temperature taken before the start of the assessment. For microvascular endothelial function, we will evaluate the maximal perfusion over the baseline perfusion (x-fold change) and the acute

reperfusion index (over the first 4 seconds of cuff release) in the nailbeds and the hand as previously described. For macrovascular endothelial function, change in the brachial artery diameter over the baseline will be calculated (% change), as previously described. When appropriate, data will be summarized using mean ( $\pm$ SEM) by group and study visit. We will use GLM for between-group factor and repeated measures (within group) factor. For post-hoc analysis, we will perform the Bonferroni test. The level of significance will be regarded as  $p < 0.05$ .

**Cognitive performance:** For cognitive assessment, all NIH Toolbox tests will be organized into two groups of fluid abilities (i.e., working memory, processing speed, episodic memory, and two aspects of executive functioning) and crystallized abilities (i.e., dependent upon past learning and experience), resulting in Standard Scores for these superordinate categories, as well as a total Composite score of all tests. We will use Standard Scores and Composite scores for analysis. These norms were previously reported to align with the age-corrected normative data for the traditional neuropsychological measures, and also because the time interval between baseline Visit 1 and final Visit 2 would not be affected by the participant's race/ethnicity or educational level. We will use GLM for between-group factor and repeated measures (within group) factor. For post-hoc analysis, we will perform the Bonferroni test. The level of significance will be regarded as  $p < 0.05$ .

**Functional magnetic resonance imaging (fMRI)** will be used to quantify patterns of activation associated with brain networks reorganization before and after treatment on each participant. Structural and functional imaging data will be acquired. Structural T1-weighted scans, T2 scans, and scans assessing tissue characterization will be acquired. Functional scans will be acquired with a single-shot EPI sequence. Functional runs will be collected using a cognitive performance task such as the N-back task, and will have a duration of 21 minutes or less. Each MRI session will be less than 2 hours within the magnet. A repeated measures design (baseline and post-TRE) will be conducted for each participant. Additional baseline data will be obtained for secondary correlations. Besides that, a sensitivity analysis testing the comparison of post-TRE only will be additionally conducted.

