**A. Specific Aims**

Our central hypothesis is that closer adherence to TRE will improve endothelial function, NVC responses, resulting in improved cognitive performance, potentially through activation of SIRT1-dependent vasoprotective pathways. The following aims are proposed:

**Aim 1: Determine the impact of TRE on microvascular endothelial function, cognitive function, and NVC responses in older adults.** Study 1 will evaluate NVC responses using functional near-infrared spectroscopy (fNIRS), electroencephalography (EEG), and dynamic retinal vessel analysis (DVA). Study 2 will evaluate peripheral micro- and macrovascular endothelial function using laser speckle contrast imaging and flow-mediated dilation approaches. Study 3 will evaluate performance in different cognitive domains using a comprehensive battery of cognitive tests.

**Aim 2: Determine the impact of TRE on circulating biomarkers and cerebrovascular endothelial cell SIRT1 activity.** Irrespective of whether the results of Aim 1 are positive or negative, we need to understand the effect of TRE on SIRT1 activity levels and related deacetylation by-products in the human participants. Study 4 To assess the effects of TRE on cellular SIRT1 activity we will treat human cerebral microvascular endothelial cells (CMVECs) with fasting serum obtained from older adults undergoing TRE and age-matched controls. We anticipate that altered SIRT1 activation will affect NO bioavailability, endothelial oxidative stress, and inflammation in CMVECs and in circulating blood. We also hypothesize that these changes will correlate the magnitude of NVC impairment and cognitive performance in older adults, and that TRF treatment I will improve these outcomes.

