**D. Research Design and Methods**

**Clinical trial design:** We will test the primary hypothesis that TRE improves NVC responses and endothelial function in older adults. This hypothesis will be tested by assessing the effects of TRE (10 hours eating window) in community dwelling older adults (55-80 years of age) in a 6-month study. At screening (Visit 0), participants will be evaluated for eligibility criteria, after obtaining informed consent. Individuals

will be asked report medications or supplements intake. Screening assessments and baseline physiological assessments may be conducted at that same visit (baseline, Visit 1) if all eligibility criteria are met, or within 4 weeks of Visit 0 (screening window) at the discretion of the investigator, when eligibility will be again confirmed. After baseline, the first fMRI and dual X-ray absorptiometry (DXA) scan visits will be performed, if the participant opts in to these measurements.

Upon completion of baseline physiologic measurements, all participants will be instructed to maintain TRE for the ensuing 6 months. Participants will be instructed on how to adhere to the TRE protocol. Participants will be evaluated at the Translational Geroscience Laboratory at the end of the protocol, at month 6 (-14/+14 days), when all physiologic assessment will be repeated (Visit 2). If participants terminate the protocol early for any reason, they will be invited to an early termination visit (ETV), which will include repeat physiologic and other evaluations same as in Visit 2. After visit 2, the second fMRI and DXA scan visits will be performed. As stated in the protocol and consent form, MRI and DXA scan visits are optional.

**Power analysis:** Based on our preliminary data analysis, a total of 27 eligible participants will provide 80% power for detecting a decrease of 7.4 in fNIRS against the null hypothesis of no change. A standard deviation of 13.1 was used in the calculation. After adjusting for a 20% dropout, the total of 32 participants will be enrolled. We will use intent-to-treat approach, wherein every participant will be included in the analysis regardless of whether participant is on or off the TRE for the final visit. To control for potential confounding, we will account for BMI, depression, the use of opiates, and other non-exclusive chronic conditions.

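### The EEG paragraph prescribes only independent-samples tests between groups, while Section D describes one arm measured twice

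*Protocol*

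**What the plan says.** **Design (Section D, clinical trial design and power analysis).** After baseline, "all participants will be instructed to maintain TRE for the ensuing 6 months". They return at month 6, "when all physiologic assessment will be repeated (Visit 2"). No allocation to a control condition is described, and the sample size is a test of a change in fNIRS against zero change.

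**EEG (Section M).** Spectral power is compared channel by channel. After a Lilliefors test, for normal data an F "test will be then used to confirm equality of variances between groups, and the two-sample" t test or its Welch version is applied. Otherwise the plan reads "For not normally distributed data, a Mann-Whitney" U "test will be used for group comparison". Benjamini-Hochberg correction follows. Neither visit nor subject appears.

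**References to controls elsewhere.** The fNIRS paragraph of Section M uses a mixed model "to assess the main effect of group (TRE vs. control) on NVC responses", and the DVA paragraph makes control versus TRE a between-group factor. Aim 2 (Section A) speaks of "fasting serum obtained from older adults undergoing TRE and age-matched controls". Section I says "Both male and female participants will be enrolled in each group". Section O gives example data labels for control and TRE participants. No section says how controls would be recruited, allocated or counted.

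**The concern.** Two-sample t, Welch and Mann-Whitney tests assume that the two sets of values come from different, independent people. Under Section D the values at hand are two readings on the same people. If those tests are run on Visit 1 against Visit 2, the within-person correlation is discarded and the standard error is wrong. The F test of equal variances has no bearing on an analysis of paired differences. If "test will be used for group comparison" instead means TRE against control, Section D supplies no one to compare with.

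EEG is the measure that Section D (Study 1) assigns to the neuronal part of neurovascular coupling. What is at stake is whether a real change in that component over six months would be detected.

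**Working it through.** **1. Which comparison was the trial sized for?** Inputs from Section D: change 7.4, SD 13.1, 27 evaluable participants, 80% power. Two-sided alpha 0.05 is assumed, because the power paragraph states neither level nor sidedness.

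- One-sample (paired) t test: noncentrality = (7.4/13.1) × sqrt(27) = 0.565 × 5.196 = 2.94. Power from the noncentral t is 0.807 at n = 27 and 0.791 at n = 26, so 27 is the smallest n that reaches 80%. The stated figure is reproduced.
- Two-sample reading with the same inputs: about 50 per group are needed. With 27 per group power is 0.53, and with 14 per group it is 0.30. The stated 27 is not reproduced.

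The sized comparison is within person, and 13.1 behaves as the SD of the change.

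**2. How do the other Section M analyses treat the two visits?**

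| Outcome | Within-person element |
|---|---|
| fNIRS | random subject effect |
| DVA | Visit 1 and Visit 2 as repeated factor |
| Peripheral endothelial function | repeated-measures factor |
| Cognition | repeated-measures factor |
| fMRI | baseline and post-TRE repeated measures |
| EEG | none |

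Removing the control factor leaves each of the others with something within person. It leaves EEG with nothing suitable.

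**3. Standard error if the tests are applied to Visit 1 and Visit 2.** With per-visit SD s, n pairs and correlation rho:

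- two-sample SE = s × sqrt(2/n)
- correct SE = s × sqrt(2(1 - rho)/n)
- ratio = 1/sqrt(1 - rho)

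The ratio is 1.00 at rho 0, 1.12 at 0.2, 1.41 at 0.5 and 1.83 at 0.7. Example at rho 0.5 with SD of change 13.1: s = 13.1/sqrt(2 × 0.5) = 13.1, two-sample SE = 13.1 × sqrt(2/27) = 3.57, correct SE = 13.1/sqrt(27) = 2.52, and 3.57/2.52 = 1.41.

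**4. Illustration of the power loss.** The protocol gives no EEG effect, SD or correlation. Assumed: the fNIRS standardised effect 7.4/13.1, n = 27, bivariate normal data, SD of change held at 13.1 so that s = 13.1/sqrt(2(1 - rho)), and one unadjusted two-sided 0.05 test. There were 60,000 simulated trials per setting.

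| rho | Paired power | Two-sample power | Two-sample type I error |
|---|---|---|---|
| 0 | 81% | 82% | 4.9% |
| 0.2 | 81% | 75% | 3.0% |
| 0.3 | 81% | 70% | 2.1% |
| 0.5 | 81% | 54% | 0.7% |
| 0.7 | 81% | 26% | 0.07% |
| 0.8 | 81% | 9% | 0.01% |

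The paired test holds its 5% level throughout.

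**The case against.** The strongest reply is that the protocol nowhere says Visit 1 and Visit 2 EEG will be compared with a two-sample test. Given the control-group wording in Sections A, I, M and O, the groups in the EEG paragraph are most naturally TRE and control. A reader might infer that Visit 1 against Visit 2 is the only comparison the protocol contemplates; the documents do not support that. EEG is then one symptom of a wider mismatch between Sections M and D, and if controls exist, a two-sample test on change scores would be valid. This stands, and it is why the design must be settled first. It does not clear the EEG paragraph. Section D provides no controls, and the paragraph does not say whether changes or Visit 2 values would be compared. A comparison of Visit 2 values alone would ignore baseline.

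The size is also open to challenge. The steep fall in the table comes partly from holding the SD of change fixed, which raises the per-visit SD as rho rises. Holding the per-visit SD fixed would show the loss mainly as paired power rising. The standard-error ratio is the same either way. The power figures are for a single unadjusted test, whereas the plan corrects across channels, so they do not describe the planned analysis.

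A reader might also infer that a null EEG result would be used to credit any fNIRS change to the vessels. The protocol says only that EEG evaluates the neuronal component. Choosing the test from a normality check, and the scale on which spectral power is analysed, are matters of preference and no part of this point.

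**Conclusion.** The point holds in limited form. The EEG paragraph fixes tests that do not fit the study in Section D: they have either no comparator or, if applied across visits, the wrong standard error. Because the protocol itself names the tests, this is not detail left to a SAP.

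If the tests are applied across visits, the standard error is too large by 1/sqrt(1 - rho). This direction rests on a positive correlation between visits, which is expected for repeat readings on one person but is not stated. At rho 0 nothing is lost; at rho 0.5 the illustrative power falls from about 81% to 54%. The error is conservative: a real EEG change could be missed, and false positives are not inflated. The actual loss cannot be fixed from the documents. EEG does not drive the sample size, so the point should be corrected but does not undermine the fNIRS calculation.

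**What to change.** 1. State in Sections D and M whether the study has one arm or a control group, and bring Sections A, I and O into line.
2. If it has one arm, replace the EEG tests with a within-person analysis for each channel: a mixed model with visit as fixed effect and subject as random effect, or a paired t test with the Wilcoxon signed-rank test as the alternative. Drop the F test of equal variances. Keep Benjamini-Hochberg.
3. If a control group does exist, say how it is formed and counted, and compare within-person changes between groups or adjust the Visit 2 value for Visit 1.

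For the single-arm design, the EEG change is one paragraph of Section M and needs no further data, since both visits are already planned. Aligning the control-group wording means edits to the other sections named.
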